### Parent-child variables

*Attachment Security: The Security Scale* [93] is a 15-item self-report questionnaire for children between the ages of 8 and 18 and measures attachment security with their parents. Children report on their attachment security with both parents separately. The scale consists of three dimensions: perceptions of responsiveness and availability of the parent, tendency to seek parental support in times of stress and the quality of communication with the parent. Children rate the items on a 5-point Likert-Scale ranging from ‘strongly agree’ (1) to ‘strongly disagree’ (5) with a higher score indicating greater perceived attachment security. Several studies indicate adequate reliability and validity [94]. Kerns, Tomich, Aspelmeir and Contreras [95] reported high internal consistencies for 10 and 12 year olds (α = 0.82, α = 0.79). Test-retest reliability over a two-week period was high (r = 0.75) [93]. The Security Scale is related to other attachment measures [95]. In a Dutch sample, internal consistency was α = 0.77 for the mother version and α = 0.85 for the father version [96].

*Generalized Trust Beliefs: Children’s Generalized Trust Beliefs* [97]. The original questionnaire assesses children’s generalized trust beliefs across three bases of trust (reliability, emotionality and honesty) in four target groups (mother, father, teacher and peers). Reliability measures the belief that parents will keep their promises. Emotionality measures the belief that parents keep their secrets confidential. Honesty measures the belief that parents are truthful. For the purpose of this study, we only use the mother and father as targets, which results in a total of 12 items. Names and situations were adjusted to fit the Dutch population. Children are presented with specific situations of fictional children and instructed to imagine that they were the children in the stories. Items are rated on a 5-point Likert scale ranging from ‘very unlikely’ (1) to ‘very likely’ (5). Reliability and validity were acceptable in earlier research (total scale 0.76, reliability subscale: 0.67, emotionality subscale: 0.62, honesty subscale: 0.65) [97]. A pilot study confirmed the usefulness and content validity of the scale with children.

To assess parenting behavior, both from the child’s and the parent’s perspective, we will use *the Ghent Parental Behavior Questionnaire* [98]. The brief child version of the GBPS has 25 items for each parent [99]. The parent version of the GBPS has 60 items and includes nine subscales: Positive parenting, monitoring, rules, discipline, inconsistent discipline, harsh punishment, ignoring, material rewarding, and autonomy. Cronbach’s α for the subscales is moderate to good [98].

*Capitalization Scale* [100]. To assess parents’ capitalization attempts to their child’s sharing of positive events, we adopted Gable et al.’s [100] capitalization scale. Parents indicate, using 5-point scales, whether they “reacted enthusiastically to their child’s sharing of a good event” (Active–Constructive), “pointed out the potential problems or down sides of the good event” (Active–Destructive), “said little, but my child knew I was happy for him/her” (Passive–Constructive), and “seemed disinterested” (Passive–Destructive). The original scale was found to be reliable and valid [100].

*Self-Control:* For a description see child adjustment measures above.

*Protective Factors Survey* [101]. The Protective Factors Survey assesses multiple protective factors against child maltreatment. The survey consists of 20 items and five subscales, namely Family Functioning/Resiliency, Child Development/Knowledge of Parenting, Concrete Support, Social Support and Nurturing and Attachment. Items are rated on a (7-point) frequency or agreement scale.

*The Confusion Hubbub and Order Scale* [102] measures environmental confusion in the home. This refers to the levels of environmental noise, crowding and disorganization in a household, in short: chaos. The questionnaire was translated into Dutch for this study, and includes 15 statements that are rated by the parents as ‘not true’, ‘quite true’ or ‘very true’. The Confusion Hubbub and Order Scale has good internal consistency (α = 0.79) and test-retest reliability (α = 0.74) [102].

*The Inclusion of the Other in the Self Scale* [103]. This Inclusion of the Other in the Self Scale is a single-item pictorial measure for closeness to others. Parents and children describe their relationship by selecting a set of two circles. The degree of overlap between the circles stands for the degree of closeness to the other person. Parents rate on the relationship with their child and children rate on their relationship with the mother and father separately. Respondents are presented with 7 different sets of circles, ranging from a set with no overlap and a long distance between the circles and a set with almost complete overlap between the circles. The circles are held constant and only the overlap increases. Validity and reliability were adequate [103]. The Inclusion of the Other in the Self Scale has not been used before to measure the parent-child relationship. Our pilot study confirmed the usefulness and content validity of the scale with children.

*Time spent together:* Parents and children are asked 9 questions about the time they spent together during the past week. For example: “How often did you have breakfast together with your mother/child last week”. Items are rated on an 8-point scale ranging from ‘not at all’, ‘one time’, to ‘every day’.

### Treatment fidelity

All treatment sessions are audio or video-recorded to ensure that the treatment protocol of the HORIZON [10, 44] was followed. Tapes are randomly selected to be coded for treatment adherence.

### Control measures

*Parental psychopathology symptoms.* To assess parental psychopathology, we will use the *Impact of Events Scale – Revised* [104]. The Dutch version ‘*Schokverwerkingslijst* (SVL-22)’ was developed by Kleber and De Jong [105]. This questionnaire consists of 22 items measuring symptoms of post-traumatic stress disorder during the last week. The Schokverwerkingslijst-22 measures three dimensions: intrusion, avoidance and hyper-arousal. Parents rate the items on a 5-point Likert-scale ranging from ‘not at all’ to ‘extremely’. The measure has high internal consistency (α = 0.88) [106]. Further, we will use the *Young Adult Self-Report* [107]. The Young Adult Self-Report will be used to assess psychopathology symptoms in parents. This questionnaire has the same format as the CBCL described above. The short version of 29 items will be used in this study to limit the amount of time needed to fill in the questionnaire. Previous research has shown that these items discriminated well between referred and non-referred subjects [108]. Items are rated on a 3-point scale ranging from ‘not true’ (0), ‘somewhat or sometimes true’(1) and ‘very true or often true’(2). Reliability and validity of the Dutch version are good [109].

*Insightfulness Assessment* [110] (only at T1). The Insightfulness Assessment is based on a semi-structured interview that evaluates the parents’ ability to seek explanations regarding the motives underlying their children’s behaviors and to talk about them in an open, complex, insightful, and accepting manner. The interview is based on the parent viewing child-parent or child-examiner interaction segments which are video-taped beforehand and answering questions about the segments. The interview transcripts will be coded on 10 rating scales and classified into one of the following four categories: Positively insightful, One-sided, Disengaged and Mixed. This represents a constellation of parental thoughts, feelings, and perceptions regarding the child’s inner experience. Each transcript is independently coded by two coders blind to any information about the study. In a previous study, inter-rater reliability ranged from 0.77 to 0.93; inter-rater reliability on the four-way Insightfulness Assessment classification system was 0.84 [36].

*Autobiographical Emotional Events Dialogues* [111] (only at T1). In the AEED parents and children participate in an emotion discussion task, in which they recall and describe an event when the child felt happy, sad, mad, and scared, respectively. They are asked to jointly describe the event and to talk about what the child felt, thought, and did during the event. Construction of the stories is scored on 7 parent scales (Shift of focus, Boundary dissolution, Acceptance and tolerance, Hostility, Involvement and reciprocity, Closure of negative feelings and Structuring of the interaction) and 7 child scales (Shift of focus, Boundary dissolution, Acceptance and tolerance, Cooperation and reciprocity, Resolution of negative feelings and Elaboration of the stories). Also, the stories are scored on adequacy of the stories and coherence. Rating scales range from 1 to 9, a higher score indicates a greater presence of that particular construct. Ratings are based on the complete session. Scores result in a classification in one of four categories: emotionally matched, emotionally unmatched: excessive, emotionally unmatched: flat or emotionally unmatched: inconsistent. Each videotaped session is independently coded by two coders (research assistants). Coders are blind for experimental condition. In a previous study, inter-rater reliability ranged from 0.87 to 0.95 [112].

*Positive filler task*: To ensure all dyads end the AEED with a positive task before they continue with the Family interaction task, we will ask the child to briefly talk about his/her favorite food or hobby with his/her parent.

*Family interaction task* [113] (only at T1). This observational instrument measures parent-child interaction and consists of four tasks in which parent and child are instructed to complete a series of interactive tasks together. The first task is a word guessing game, in which parent and child take turns in guessing what word/picture appears on the card of the other. The second task involves getting marbles into designated holes in a labyrinth. In the third task, parent and child have to plan a pretend birthday party. The final task is constructing different patterns of pieces that match given designs. Nine rating scales are used for this study: 3 parent scales (positive responsiveness, anger and hostility, quality of assistance), 3 child scales (persistence and diligence; anger, defiance and frustration; expression of positive affect) and 3 dyadic scales (collaboration and teamwork; positive affect; negative affect/conflict). Rating scales range from 1 to 5 and a higher score indicates a greater presence of that particular construct. Ratings are based on the complete session. Each videotaped session is independently coded by two coders (research assistants). In a previous study, inter-rater reliability ranged from 0.63 to 0.73 [113].

*Severity and intensity of IPV.* To assess the severity and intensity of the violence that children have been exposed to, we will use a combined measure including items from the Conflict Tactics Scale [114], the Conflict Tactics Scale parent child [114], the Parents Report of Traumatic Impact [115]; and the Adverse Childhood Experience Questionnaire [116]. This combined questionnaire has been used in a previous study on the effectiveness of a psycho-educational prevention program for children exposed to IPV [117]. The questionnaire covers the topics of duration of the violence, the nature of the arguments in the relationship with the (ex-partner), followed by items from the Conflict Tactics Scale parent child and Parents Report of Traumatic Impact about problems between parent and child, and traumatic events the child has experienced. The questionnaire also includes items about traumatic experiences in parents’ own childhood.

*New IPV incidents:* Parents and children are asked 8 questions if any new IPV incidents or other stressful events occurred.

### Statistical analyses and sample size calculation

All variables are measured on at least an ordinal scale. All scale scores will be examined for normality. Should we observe deviations, steps will be taken to ensure optimal estimation of parameters in our analyses. The proposed study includes a nested structure, because individuals are treated within groups. Following the recommendations by Peugh [118], we will calculate design effects to assess group-level dependency and examine whether multi-level modeling is required. To ensure comparability of the randomized conditions, we will control for duration and severity of the IPV [45], parental psychopathology [46], and new incidents of IPV. Power calculations were performed using the program G*power 3 [119], assuming that individual-level effects can be treated as independent data. We determine required sample size to be 100 parent-child dyads, achieving statistical power of at least .80 for the primary and secondary objectives, as described in more detail in the following paragraphs. We will test for the randomness of missing data. If this is the case we will use multiple imputation.

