### Randomization, blinding, and treatment allocation

Recruitment will take place in three mental health centers in The Netherlands. For each center families are referred for treatment after children have been exposed to interparental violence. As soon as a group of approximately 8 families have met the inclusion criteria for participation in the HORIZON group treatment (see Inclusion and Exclusion Criteria), and after informed consent is obtained, the families participating in the study will participate in T1 measurements. Parents and children are asked to fill out questionnaires and to participate in two observational tasks. Additionally, the parent is interviewed about the observational tasks. After T1, the group will be randomly assigned to one of the four treatment conditions (see Fig. 1) by an independent researcher using a randomization procedure with lottery drawings. Conditions 1 & 2 will start one week after T1, and conditions 3 & 4 will start seven weeks after T1. One week (T2) and six months (T3) after the end of the program, parents and children are again invited to fill out questionnaires (see Fig. 2). At all assessments the teacher is also sent a questionnaire. Typically, the intervention group consists of two child groups (4–7 years and 8–12 years, respectively) and one parent group. Usually there is only one parent group, because families often have more than one child who participate in the intervention, and because parents without visitation rights do not participate. The child groups receive treatment at the same time but in different rooms. The parents of children in both groups receive group sessions on the same time. Because it is not feasible for participating trauma centers to start four interventions at the same time, we cannot randomly assign individual children or parents to one of the four conditions. Therefore, we choose randomization by group just before the start of the group therapy and after T1. Parents and children are blind to treatment condition until randomization is carried out just before the (preparatory) program starts. Clinicians will be blind for treatment condition until all families are indicated for treatment. The assessments include videotaped observational tasks. Independent research assistants will code these videos. All coders are blind for treatment condition. Sometimes it will take a few months before families can participate in one of the four group interventions, due to waiting lists and enrollment numbers to form treatment groups. If necessary, parents and children will receive family or individual stabilization intervention during this time. Independent of their experiences with treatment preceding participation in the HORIZON, all participating families will be measured at T1 at the same time to ensure comparability of the families in the study.

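### Whole groups are randomised, but whether the primary analysis models them depends on a design effect estimated from about 12 groups

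*Protocol article*

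**What the plan says.** The protocol article, under *Randomization, blinding, and treatment allocation*, explains that the centres cannot start four interventions at once and that "we cannot randomly assign individual children or parents to one of the four conditions". It continues: "Therefore, we choose randomization by group just before the start of the group therapy and after T1". The trigger for forming a group is given as "As soon as a group of approximately 8 families have met the inclusion criteria". An intervention group normally holds two child groups, split by age, and one parent group. There is usually a single parent group partly because "families often have more than one child who participate in the intervention".

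Under *Statistical analyses and sample size calculation*, the article recognises the nesting: "The proposed study includes a nested structure, because individuals are treated within groups". It attributes the nesting to treatment delivery and does not mention that these groups are also what is randomised. The response is conditional: "we will calculate design effects to assess group-level dependency and examine whether multi-level modeling is required". No threshold is stated. Power was calculated "assuming that individual-level effects can be treated as independent data".

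Under *Primary objective* in the same part of the article, the primary analysis is a multiple regression on one dummy per parental component and their interaction. It is run separately for trauma, internalizing and externalizing symptoms, and no group term is listed. The stated power is .84 with 100 children, five predictors, f² = .15 and alpha .05.

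**The concern.** The two parental components vary only between randomised groups. Information about them therefore comes from differences between groups, whatever ICC is estimated. If the group term is left out and outcomes within a group are correlated, the standard errors of both component effects and of their interaction are too small.

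The protocol lets the data decide whether this matters, but about 12 groups say little about an ICC. A low estimate is weak evidence that clustering is absent, yet it would send the primary analysis to ordinary regression with about 94 error degrees of freedom, when about 8 exist at group level. The three primary outcomes are analysed separately, so the check could also leave different models in force for different outcomes. At stake is the type I error of the trial's main tests.

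**Working it through.** **Inputs.** From the protocol article: 100 children, groups of about 8 families, four conditions, f² = .15, alpha .05, five predictors. Not in the article, hence assumed: the group ICC (0 to .15), the design-effect cut-off (1.1, 1.5 or 2) and any extra correlation between siblings (.3).

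**1. Units.** 100 / 8 = 12.5, so about 12 groups, or 3 per condition, if each supplies about 8 study children. Group-level df = 12 − 4 = 8. Ordinary regression with five predictors has 100 − 5 − 1 = 94.

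**2. The stated power.** Noncentral F with λ = f² × N:
- five predictors: λ = .15 × 100 = 15, df 5 and 94, power .843 (stated .84)
- four predictors: λ = 15, df 4 and 95, power .874 (stated .87)
- two predictors: λ = .10 × 100 = 10, df 2 and 97, power .803 (stated .80)

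All three reproduce, under independence only.

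**3. False-positive rate.** Null trials were simulated with 12 groups of 8 (96 children), 40,000 per setting, testing a component main effect. With balanced groups the other component and the interaction behave the same way. The Monte Carlo standard error near 5% is √(.05 × .95 / 40,000) ≈ 0.1 percentage point.
- *Ordinary regression:* pooled residual variance, 96 − 4 = 92 df.
- *Group-level test:* between-group mean square (MSB), 8 df.
- *Screened rule:* with MSW the within-group mean square, estimate ICC = (MSB − MSW) / (MSB + 7 × MSW), set to 0 if negative. The design effect is 1 + 7 × ICC. Use ordinary regression below the cut-off, otherwise the group-level test.

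Rejection rates (%). In the screened columns the first figure has condition in the model when the ICC is estimated, and the second does not.

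| True ICC | Ordinary | Group-level | Screen 1.1 | Screen 1.5 | Screen 2 |
|---|---|---|---|---|---|
| 0 | 4.9 | 5.1 | 3.5 / 3.2 | 4.3 / 4.1 | 4.8 / 5.0 |
| .02 | 6.5 | 5.0 | 3.9 / 3.6 | 5.2 / 4.5 | 6.1 / 5.8 |
| .05 | 9.3 | 4.8 | 4.5 / 4.2 | 6.3 / 5.3 | 8.1 / 7.6 |
| .10 | 13.8 | 4.9 | 5.1 / 4.6 | 7.1 / 5.5 | 10.2 / 8.6 |
| .15 | 18.1 | 5.0 | 5.2 / 4.9 | 6.9 / 5.5 | 10.6 / 8.3 |

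**4. How often the group is dropped** (condition in the model). At a true ICC of .05, ordinary regression is kept in 38%, 65% and 87% of trials for cut-offs 1.1, 1.5 and 2. At ICC .10 it is kept in 21%, 44% and 71%.

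**5. Degrees of freedom.** Always fitting the mixed model is not enough if it is tested against the normal distribution. That gives 5.0%, 6.0%, 7.2% and 8.0% at ICC .02, .05, .10 and .15.

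**6. Power with clustering.** Take λ = 15 / (1 + 7 × ICC), keeping 94 error df. At ICC .02 the design effect is 1.14 and power .785; at .05, 1.35 and .70; at .10, 1.70 and .58; at .15, 2.05 and .49. This is a rough guide and optimistic on degrees of freedom.

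**7. Siblings.** Suppose half of 8 families bring two children. A group then has 12 children, so 96 children fill 8 groups, leaving 8 − 4 = 4 df and a t critical value of 2.78. With an extra sibling correlation of .3 and group ICC 0, the design effect is 1 + (8/12) × .3 = 1.20 and ordinary regression rejects at 7.4%. At group ICC .05 it rejects at 14.3%. The group-level test stays at 5.0% in both cases.

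**The case against.** The strongest reply is that the protocol does not ignore clustering. It names the nesting, cites a source for its check and commits to carrying it out. That source may supply a cut-off, and an analysis plan that is not shown may supply the threshold and the degrees-of-freedom method. With a low cut-off the screened rule stays near or below 5%.

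Much of this stands. A reader might infer that clustering will often be dropped and the error rate will be inflated. The documents do not support that, because they give neither a cut-off nor an ICC, and the result turns on both. A reader might also take the 7 to 18% for ordinary regression as the plan's error rate. It is the rate only if the check were skipped or always favoured ordinary regression. The absence of a threshold or of a named df method is not the fault either, since a journal article may leave both to a fuller document.

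A third inference is that ignoring siblings is a separate defect of equal weight. The article says siblings often attend together, but not that both enter the analysis as independent children. Siblings also sit inside the same randomised group, so a retained group term already protects the component tests. Their correlation raises the estimated group design effect too, which makes the check more likely to call for multi-level modelling.

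What the reply does not answer is the rule itself. Making the group term conditional on an estimate is a stated choice, and no citation makes about 12 groups enough to show that clustering is absent.

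**Conclusion.** The point holds in this form: groups are the unit of randomisation, so whether the primary analysis respects them should not depend on an estimated design effect. The likely harm ranges from none (ICC 0, or a cut-off near 1.1 with small-sample df) to a false-positive rate roughly double the nominal 5% (cut-off 2, ICC .10 to .15). A cut-off of 1.5 lies between. These sizes rest on the assumed ICCs and cut-offs, on 12 equal groups of 8, and on a group-level t test whenever the screen retains clustering. The direction is secure and the exact size is not. Because the rule governs both component tests and their interaction on all three primary outcomes, and the remedy is simple, it should be changed before any outcome data are analysed.

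**What to change.** Delete the screening step. State that every analysis of the component effects and their interaction will include a random intercept for the randomised intervention group (the whole unit, covering both age groups and the parent group), or will be done on group means. Use a small-sample method such as Kenward-Roger, or group-level df. Report the ICC and design effect descriptively. A family term where siblings take part is a secondary refinement. Restate power with an assumed ICC and the expected number of groups.

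The cost is mainly wording; the *Trial status* section says inclusion had only just begun. The statistical price is wider intervals. The t critical value is about 2.31 with 12 groups against 1.99 for ordinary regression, and larger with fewer groups. Power falls below the stated .84, which was always conditional on independence.

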### Secondary objectives

Our second goal is to evaluate the effects of these two parental treatment components on child adjustment. Our third goal is to investigate mechanisms underlying the efficacy of treatment for children who have been exposed to IPV by examining associations between: child symptoms, on the one hand, and, 1) child responses (i.e., child emotional, behavioral, and cognitive responses, 2) parental availability and 3) parent-child interaction, on the other.

Our fourth goal is to examine specific hypotheses of change. Specifically, we will test whether, as predicted, the preparatory program leads to increased parental availability and whether the parent-child interaction sessions lead to improved parenting behavior. Also, we will explore whether these changes lead to a reduction in symptoms.

To ensure comparability of the randomized conditions, we will control for duration and severity of the IPV [45], parental psychopathology [46], and new incidents of IPV.

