### Primary objective

The first goal of the present study is to examine the efficacy of two parental components that complement a TF-CBT-based core treatment for children who have been exposed to IPV. Therefore, a multiple regression analysis will be executed with two dummy variables as independent variables, representing both parental components (dummy 1 = parent preparatory program present vs. absent; dummy 2 = parent-child interaction sessions present vs. absent) and their interaction. Dependent variables are child symptoms (primary outcomes) at the three time points (T1, T2, and T3) clustered into 1) Trauma symptoms, 2) Internalizing symptoms, 3) Externalizing symptoms. Analyses will be independently executed for the three dependent variables. Because children in each group receive intervention, a medium effect size is expected (f^2^ = .15). With a maximum of five predictors and an alpha of .05, we achieve a power of .84 with 100 children included in the study.

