### Ethical considerations

The study protocol has been approved by the Medical Ethics Committee of the VU University Medical Center in Amsterdam, the Netherlands (METC VUmc 2011/101/NL39277.029.12). All substantial amendments will be presented to the METC and to the competent authority. Non-substantial amendments will not be notified to the accredited METC and the competent authority, but will be recorded and filed by the sponsor, ZonMw, the Dutch organization for healthcare research and innovative care. All changes will be described and discussed in the publications of the study results.

The HORIZON has been used to treat children who have experienced IPV for more than 10 years in several children and youth treatment centers in the Netherlands and does not seem to involve risks for participants. Nevertheless, should a child or a parent seem adversely affected by therapy, questionnaires or observational tasks as observed by the researchers or therapists, it may be decided to (temporarily) discontinue participation in this study. Participants can leave the study at any time for any reason if they wish to do so without any consequences. Withdrawal of participants from the study will have no impact on their treatment. Participants who withdraw from the study will not be replaced, because there is no place for them in the therapy groups, and it is not possible for parents and children to start at a later time during treatment. Should participants withdraw from the treatment, these parents and children will be followed according to the intention to treat principle. They will be asked fill in the questionnaires and the observational tasks.

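### The stated powers of .84, .87 and .80 hold only for 100 independent children, but whole treatment groups are randomised, so the unconditional claim of at least .80 is not supported

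*Protocol article*

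**What the plan says.** In the Protocol article, the section on randomization, blinding and treatment allocation explains that centres cannot start four interventions at once, so individuals cannot be allocated: "Therefore, we choose randomization by group just before the start of the group therapy and after T1". A group is formed once about 8 families qualify. The same section adds that families often bring more than one child and that there is usually a single parent group.

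The section on statistical analyses and sample size calculation acknowledges that individuals are nested in groups. It plans to calculate design effects and then decide whether a multilevel model is needed. The power calculation itself, however, was made "assuming that individual-level effects can be treated as independent data". It concludes: "We determine required sample size to be 100 parent-child dyads", "achieving statistical power of at least .80 for the primary and secondary objectives".

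For the primary objective, "a medium effect size is expected (f^2^ = .15"), and then: "With a maximum of five predictors and an alpha of .05, we achieve a power of .84 with 100 children included in the study". The regression contains two component dummies and their interaction. The trial objectives and the statistics section both add that "we will control for duration and severity of the IPV [45], parental psychopathology [46], and new incidents of IPV". The two secondary calculations give .87 (4 predictors, f² = .15) and .80 (2 predictors, f² = .10), each with 100 participants.

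On losses, the section on ethical considerations states: "Participants who withdraw from the study will not be replaced".

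**The concern.** Both experimental factors are assigned to groups, not to children. Children in a group share therapists, sessions and a parent group, and some share a family. Any positive correlation of outcomes within a group reduces the information that 100 children carry about a component effect. The sample size calculation sets that correlation to zero, although the same section recognises the nesting.

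Two further inputs sit uneasily with the plan. The named control variables, added to the three design terms, exceed the stated maximum of five predictors if they are counted. The calculations also use all 100 participants although withdrawals are not replaced.

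At stake is how the result will be read. A reader who trusts at least .80 would give a non-significant component effect more weight against that component than the design may justify.

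**Working it through.** **Inputs from the protocol.** N = 100; alpha = .05; f² = .15 with 5 predictors, f² = .15 with 4, f² = .10 with 2; groups of about 8 families. 100/8 = 12.5, so about 12–13 groups over four conditions, about 3 each.

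**Input not in the protocol.** The ICC. A range of .01 to .10 is assumed below.

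**1. Reproducing the stated figures.** Power of the regression F test is P(F′ > F crit), with F′ noncentral F, noncentrality λ = f² × N, df1 = u, df2 = N − u − 1.

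- u = 5, λ = 15, df2 = 94: .843 (stated .84)
- u = 4, λ = 15, df2 = 95: .874 (stated .87)
- u = 2, λ = 10, df2 = 97: .803 (stated .80)

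The arithmetic is right for 100 independent observations.

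**2. Adding the grouping.** Design effect DE = 1 + (8 − 1) × ICC; effective N = 100/DE, put into the same formula.

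| ICC (assumed) | DE | Effective N | Primary, u = 5 | Associations, u = 4 | Mediation, u = 2 |
|---|---|---|---|---|---|
| 0 | 1.00 | 100 | .84 | .87 | .80 |
| .01 | 1.07 | 93.5 | .81 | .85 | .77 |
| .02 | 1.14 | 87.7 | .78 | .82 | .74 |
| .05 | 1.35 | 74.1 | .69 | .73 | .66 |
| .10 | 1.70 | 58.8 | .56 | .61 | .55 |

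The associations column is an upper bound on the loss. Those predictors (child responses, parental availability, parent-child interaction) vary mainly between individuals, and full inflation overstates the effect of clustering on them.

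**3. Break-even ICC.** Power of .80 needs N = 91.2 for the primary analysis, so DE may be at most 100/91.2 = 1.096 and the ICC at most .096/7 = .014. Mediation needs 99.4, so the ICC may be at most .006/7, about .001. The 4-predictor analysis needs 84.4, which allows .026 even with full inflation.

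**4. Sensitivity to group size.** For the primary figure at ICC .05 and .10: 5 study children per group give .75 and .67; 12 per group give .61 and .45.

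**5. Predictor count, with no clustering.** Three design terms plus IPV duration and severity as one score, parental psychopathology and new incidents make 6: power .81. With duration and severity separate there are 7: .785.

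**6. Withdrawals.** From step 3, with no clustering, the primary figure drops below .80 once fewer than 92 children are analysed, and the mediation figure once one is lost. At an assumed 20% loss (N = 80) the primary figure is .73.

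**7. One component's main effect, group as unit.** Assume 12 groups of 8 (N = 96), df = 12 − 4 = 8, SE = √((4/96) × DE) in standard-deviation units, noncentral t with noncentrality d/SE.

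- If f² = .15 is one component's effect, then for a balanced factor d = 2√.15 = .77. At ICC .05, SE = .237 and power is about .82; at ICC .10, SE = .266 and power is about .72.
- If d = .5, which is my assumption and not in the protocol (f² = .5²/4 = .0625): .58 at ICC 0, .46 at ICC .05, .38 at ICC .10.
- The effect detectable with 80% power is about d = .76 at ICC .05 and .85 at ICC .10.

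**The case against.** **The assumption is disclosed and clustering will be checked.** Both are true, and the reader is told the basis of the figures. But a design effect calculated at analysis does not restore power. If it leads to a multilevel model, the power statement no longer describes the analysis performed.

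**The size of the shortfall rests on an ICC nobody has stated.** This stands. The documents show that the claim depends on an ICC near zero; they do not show what the ICC is.

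**The predictor count is not decisive.** This largely stands. The protocol describes one combined instrument covering severity and duration, so the minimum is 6, which still gives .81. A reader might infer that the plan's model must have at least 7 predictors and fails on that ground alone; the text does not establish that.

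**The .84 may not be an omnibus test.** A reader might infer that it tests all predictors jointly, covariates included. The protocol does not say so. Testing five predictors within a model of 7 terms gives .842, so the figure fits either reading. On the second, extra covariates cost almost nothing.

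**The design might still be adequate for a component.** A reader might take the d = .5 figures as proof that it is badly underpowered. That effect size is not the plan's. With f² = .15 read as one component's effect, power is about .82 at ICC .05. The protocol does not state that reading, and its .84 does not come from it: a one-predictor test at f² = .15 and N = 100 would give .97.

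**Attrition is thinly evidenced.** The 20% is assumed, treatment drop-outs are to be followed up, and multiple imputation is planned. Imputation does not replace the information in missing outcomes, but this point is secondary.

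**Conclusion.** The point holds. The three powers are computed correctly from an input that the allocation method contradicts. With groups of 8, at least .80 for all objectives requires an ICC no higher than about .001, and for the primary objective alone about .014 with five predictors. At an assumed ICC of .05 the primary figure is about .69 and the mediation figure about .66; at .02 they are .78 and .74. Shared therapy, a shared parent group and siblings make a near-zero ICC hard to presume.

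The size rests on the assumed ICC, on about 8 study children per group, and on applying one design effect to all terms. That last step suits the group-assigned component terms but overstates the loss for individual-level predictors, so the .87 figure is the least affected.

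The predictor count and the missing attrition allowance are supporting points that narrow an already small margin. It would go too far to say that the trial could detect only a large effect, or that it cannot reach .80 for a component: that depends on the ICC and on what f² = .15 refers to, and the protocol settles neither.

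**What to change.** Keep 100 dyads and rewrite the sample size paragraph:

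- Delete the unconditional claim of at least .80 for the primary and secondary objectives.
- State which test, and which effect, f² = .15 refers to.
- Give power, or the minimum detectable effect, for each component's main effect with the treatment group as the randomised unit. Use about 12–13 groups, group-level degrees of freedom and an ICC range labelled as an assumption.
- Use the actual number of predictors, saying whether duration and severity enter as one term or two, and include an attrition allowance.
- Present the .87 separately, as a calculation for mainly individual-level predictors.

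The cost is one reworded paragraph and less favourable stated power. No extra participants are needed for this correction.
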